### Procedure

Potential participants will be provided with a participant information sheet by email or post (depending on individual preference) prior to attending for their assessment session. They will be given at least 24 hours to consider their participation and will have the opportunity to ask questions (via email or telephone) prior to the session.

Written informed consent will be obtained at the start of the assessment session, prior to the completion of any study assessments.

Next, participants will complete a series of questionnaires on:

Demographics, including year of birth, sex assigned at birth, ethnicity, recruitment stream, Scottish Index of Multiple Deprivation, level of education, employment status and household income.Health behaviours, using the General Practice Physical Activity Questionnaire^38^ and the WHO’s Alcohol, Smoking, and Substance Involvement Screening Test.^39^Long-term conditions, using the LTCs listed in table 1.Chronic pain, using the UK Biobank Pain Web Questionnaire.^40^Adverse childhood experiences, using the CAPE ACE questionnaire (in the final stages of development).Current medication.

Then participants will have their height and weight recorded.

Next, we will begin QST based on a protocol devised by the German Research Network on Neuropathic Pain,^41^ with the addition of a conditioned pain modulation (CPM) paradigm. Each test will be performed bilaterally, with the exception of the CPM test, which will be performed on one side only.

Thermal detection and pain thresholds will be measured at the forearm or hand using a Modular Sensory Analyser with a standard 25×50 mm thermode (Somedic SenseLab, Sweden). Starting from a baseline temperature of 32°C, we will use the ramp method with a rate of change of 1°C/s. The lower and upper cutoffs will be 10°C and 50°C, respectively. Participants will be instructed to press a button at the appropriate point for each test; for the cold detection threshold and warm detection threshold, this will be when they ‘first feel a [cold/warm] sensation’ at the test site; and for the cold pain threshold and the heat pain threshold, this will be when they ‘first feel something that is painfully [cold/warm]’ at the test site. For each parameter, we will take three measurements and calculate the mean. The result of the TSL test, in which alternating cold and warm stimuli are applied, will be the number of paradoxical heat sensations reported (ie, where cold is reported as warm and vice versa).The mechanical detection threshold will be measured at the forearm or hand using a standardised calibrated set of von Frey filaments (Somedic SenseLab, Sweden) that exert forces of 0.63 mN to 235.36 mN on bending. With their eyes closed, participants will be asked to verbally report when they feel something touch the test site. Using the method of limits, we will take five detection threshold measurements and report the geometric mean.The mechanical pain threshold will be measured at the forearm or hand using calibrated weighted PinPrick stimulators (MRC Systems, Germany) that exert forces from 8 mN to 512 mN. With their eyes closed, participants will be asked to verbally report when they feel something sharp at the test site. Using the method of limits, we will take five pain threshold measurements and report the geometric mean.Stimulus response functions will be measured at the forearm or hand using the same PinPrick stimulators as described above and three light tactile stimulators: cotton wisp exerting a force of ~3 mN, a cotton wool tip attached to an elastic strip exerting a force of ~100 mN and a standardised brush (Somedic SenseLab, Sweden) exerting a force of ~300 mN. Stimuli will be applied in a pseudorandom sequence (consistent across all participants) with approximately a 10 s interval between stimuli. With their eyes closed, participants will be asked to verbally report a pain score for each stimulus on a numerical rating scale of 0 to 100. Mechanical pain sensitivity will be calculated as the geometric mean of the pain scores for all pinprick stimuli. Dynamic mechanical allodynia will be calculated as the geometric mean of the pain scores for all light tactile stimulators.Wind-up ratio (WUR) will be measured at the forearm or hand using the 256mN PinPrick stimulator. A single stimulus will be applied followed by a series of 10 stimuli to the same area. With their eyes closed, participants will be asked to verbally report two pain scores on a numerical rating scale of 0 to 100, one for the single stimulus and one for the series of 10. We will repeat this five times. The WUR will be calculated as the mean pain score for the series divided by the mean pain score for the single stimulus.The vibration detection threshold (VDT) will be measured at a bony prominence at the wrist or elbow using a 64 Hz Rydel-Seiffer graded tuning fork (Ragg Tuning Forks, UK). With their eyes closed, participants will be asked to verbally report when they feel the vibration sensation stop at the test site. We will take three measurements and calculate the mean.The pressure pain threshold (PPT) will be measured at the thenar eminence with an algometer (Somedic SenseLab, Sweden). Participants will be asked to verbally report when they ‘first feel pain’ at the test site. We will take three measurements and calculate the mean.CPM will be measured using the cold pressor test. The participant will be asked to lower their non-dominant hand into a cold water bath at 10°C±2°C (the conditioning stimulus). The water temperature will be generated by a Grant LTC4 refrigerated circulating bath (Grant Instruments, UK). After 20 s, we will measure two modalities of test stimuli on the dominant arm; PPT followed by HPT, as described above. We will take three measurements of each and calculate the mean. CPM will be reported as an absolute value (the mean PPT or HPT prior to the conditioning stimulus minus the mean PPT or HPT during the conditioning stimulus) and as a percentage change (absolute CPM divided by the mean PPT or HPT prior to the conditioning stimulus). Thus, a negative CPM value will indicate CPM-induced pain inhibition.^42^ We will also measure the duration of time that the hand was submerged in the cold water bath (up to a maximum of 120 s) and ask the participant to verbally report a pain score for the water bath on a numerical rating scale of 0 to 100.

Finally, participants will complete a questionnaire on study acceptability, using a questionnaire adapted from Sekhon *et al*.^43^

There is no planned follow-up for this study.

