### Sample size calculation

This is a feasibility study, and therefore a formal sample size calculation is not required. However, preliminary data from this stage will be used to determine the sample size required for a future definitive study. Whitehead *et al* (2016) suggested that a sample size of 10 per treatment arm in the pilot phase would provide enough preliminary data to determine the sample size needed to detect a medium effect in a full interventional trial.^44^ While this study is not interventional, we believe the principles to be transferable, and therefore, we will aim to recruit 40 study participants, with 10 in each group.

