### Statistical analysis

The primary aim of the ACE-MAP study is to assess the feasibility and acceptability of the proposed study procedures. Recruitment feasibility will be assessed per stream by calculating the overall recruitment rate (number of participants successfully recruited to the study per week) and the recruitment proportion (number of participants successfully recruited to the study divided by the number of potential participants approached). Acceptability will be assessed with a modified version of an acceptability questionnaire developed by Sekhon *et al*^43^ administered to study participants at the end of the assessment session. The data will be presented as counts and proportions, with free-text comments presented as either themes or original anonymised quotes.

The secondary aim is to generate preliminary data to understand the impact of ACEs on QST thresholds in people with multimorbidity and/or chronic pain. Descriptive statistics will be generated on all groups of data (demographics, LTCs, chronic pain, ACEs, medication and QST parameters). We will perform exploratory analyses, such as investigating the association between the number of ACEs experienced and individual QST parameters, and how these relationships vary based on multimorbidity/chronic pain status, using a range of statistical techniques (eg, χ^2^ tests, Student’s t-tests, regression analysis). These analyses will inform the project design and sample size calculation for a subsequent definitive study.

All statistical analyses will be performed in R V.4.2.2 using the RStudio integrated development environment (RStudio Team, Boston, USA).

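### The TSL result is named a count of paradoxical heat sensations, but its definition also counts warm felt as cold, so one number pools two opposite misperceptions.

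*Protocol article*

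**What the plan says.** The Procedure section lists the sensory tests and gives each one a result. For the TSL test the text reads: "The result of the TSL test, in which alternating cold and warm stimuli are applied, will be the number of paradoxical heat sensations reported". A bracket then defines what is counted: "the number of paradoxical heat sensations reported (ie, where cold is reported as warm and vice versa". No other TSL result is named, and no other section narrows the definition or separates the two directions.

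The same section gives the source of the procedures: "Next, we will begin QST based on a protocol devised by the German Research Network on Neuropathic Pain". That source is cited but not reproduced.

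Under Statistical analysis, the exploratory work includes "investigating the association between the number of ACEs experienced and individual QST parameters". It also looks at how these relationships vary with multimorbidity and chronic pain status, and the results are to inform the design and sample size of a definitive study.

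**The concern.** The bracket opens with 'ie', so it is a definition and not an example. In this sentence 'vice versa' can only mean that warm is reported as cold. A participant who reports cold has not reported heat, paradoxical or otherwise. The name therefore covers one direction of error while the rule counts two.

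What is at stake is the meaning of one parameter. Anyone who reads the result by its name will take it as cold felt as warm, when part of it, of unknown size, may be the opposite error. If only the total is written down, the two parts cannot be separated later, because each participant attends once and no follow-up is planned. The pooled number would then enter the ACE analyses, and possibly the planning of the definitive study, under a name that describes only part of it.

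**Working it through.** The protocol gives no figure on this point, so there is nothing to reproduce. The check is a comparison of name and rule, followed by simple algebra on assumed rates.

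**1. Name against rule.** Let a be the number of cold stimuli reported as warm and b the number of warm stimuli reported as cold.

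- Count described by the name: a
- Count scored by the bracket: a + b

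The two agree only if b = 0. With assumed counts a = 1 and b = 2, the name gives 1 and the rule gives 3.

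**2. Size of the difference.** Use c and w for the chances per pulse of cold felt as warm and of warm felt as cold. Assume n pulses of each kind; the text says that the stimuli alternate but gives no numbers.

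- Expected count by the name: n × c
- Expected count by the rule: n × (c + w)
- Ratio of rule to name: (c + w)/c = 1 + w/c

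If w = c/2 the recorded count is 1.5 times the named one; if w = c it is 2 times. With w near zero it is hardly changed.

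**3. Effect on a contrast between two groups.** The ratio by the name is c₁/c₂. The recorded ratio is (c₁ + w₁)/(c₂ + w₂), which is a weighted average of c₁/c₂ and w₁/w₂ with weights c₂/(c₂ + w₂) and w₂/(c₂ + w₂). Its direction of error therefore depends on whether w₁/w₂ is below, equal to or above c₁/c₂. Take c₁ = 10% and c₂ = 5%, so that the ratio by the name is 2.0. All rates here are assumptions.

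| w₁ | w₂ | Recorded ratio | Against 2.0 |
|---|---|---|---|
| 5% | 5% | 15%/10% = 1.5 | diluted |
| 10% | 5% | 20%/10% = 2.0 | unchanged |
| 15% | 5% | 25%/10% = 2.5 | exaggerated |

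Nothing in the document says which row is nearest to the truth.

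**The case against.** The strongest reply is that the text proves a mismatch and no more. The bracket is an explicit rule that can be applied, and the sentence alone does not show whether the name is too narrow or the bracket too wide. That is correct. The document's own words establish the contradiction, but not which side the authors meant.

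A second reply is that this is a condensed article. A short gloss for general readers may be loose wording, and the scoring sheet, which is not shown, may already record the direction of each report. This is possible, but nothing in the document says so. A general reference to a published protocol does not override a scoring rule stated in the text. Nor is this a detail left out for brevity: the rule is given, and it conflicts with its own name.

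A third reply is that little depends on it. This also stands. The primary aim is feasibility and acceptability; the hypothesis concerns sensory thresholds, and this count is not a threshold. The sample size does not depend on it either: "This is a feasibility study, and therefore a formal sample size calculation is not required".

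A reader might infer two stronger points, and the document supports neither:

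- **That real differences will be diluted.** This holds only if the reverse error varies proportionately less between groups than the named one. The table under the working shows the contrast unchanged or exaggerated under other assumptions.
- **That the parameter could not be compared with other studies.** This needs the definition used elsewhere, including in the cited network protocol, which is not at hand.

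**Conclusion.** The contradiction is real and lies within a single sentence. As written, the TSL result adds two opposite misperceptions and carries the name of one. With equal numbers of cold and warm pulses, the inflation relative to the name is 1 + w/c. Its size is unknown because the document gives neither rate, and the direction of any effect on group or ACE-level contrasts is likewise unknown.

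The contradiction itself rests only on the ordinary meaning of the sentence. The multiplier rests on the assumption of equal pulse numbers, and the worked ratios on assumed rates. It is not established that scoring at the site departs from the name, since the record form is not shown.

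This is a minor point. It touches one exploratory secondary parameter in a study that aims for 40 participants. The feasibility and acceptability outcomes are unaffected.

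**What to change.** First confirm which scoring rule is used at the sessions. Then:

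- Delete the three words 'and vice versa', so that only cold stimuli reported as warm or hot count as paradoxical heat sensations.
- If the reverse error is of interest, record warm stimuli reported as cold as a separate count under a different name.
- For sessions already held, re-derive the count if the direction of each report was noted. If only the total was kept, report it as a pooled count of thermal misperceptions.

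The cost is a three-word edit and, if the form does not already show direction, one extra column. No change to the test itself, the number of participants or the other analyses is needed.

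### Mechanical pain sensitivity and dynamic mechanical allodynia are geometric means of 0–100 ratings, so a single rating of 0 sets the whole score to 0, and no zero rule is stated

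*Protocol article*

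**What the plan says.** All the scoring rules are in the Procedure section of the protocol article.

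- Ratings: participants "verbally report a pain score for each stimulus on a numerical rating scale of 0 to 100".
- Stimuli: "calibrated weighted PinPrick stimulators (MRC Systems, Germany) that exert forces from 8 mN to 512 mN", and "three light tactile stimulators: cotton wisp exerting a force of ~3 mN", with a cotton wool tip (about 100 mN) and a brush (about 300 mN) as the other two.
- Mechanical pain sensitivity (MPS): "Mechanical pain sensitivity will be calculated as the geometric mean of the pain scores for all pinprick stimuli".
- DMA: "Dynamic mechanical allodynia will be calculated as the geometric mean of the pain scores for all light tactile stimulators".
- Wind-up ratio (WUR): at 256 mN, "participants will be asked to verbally report two pain scores on a numerical rating scale of 0 to 100". The first score rates a lone stimulus and the second a train of ten, and there are five runs. Then "The WUR will be calculated as the mean pain score for the series divided by the mean pain score for the single stimulus".

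The article gives no added constant, replacement value or exclusion rule for ratings of 0, and no rule for a zero WUR denominator. The Procedure section describes the sensory testing as based on a cited network protocol, which is not shown. The Statistical analysis section relates the number of adverse childhood experiences to individual sensory parameters, examines how this varies by multimorbidity and chronic pain status, and uses these analyses to inform the design and sample size of a later study.

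**The concern.** A geometric mean suits positive quantities measured on a ratio scale. The same section uses it for the mechanical detection and mechanical pain thresholds. Those are forces that are always above zero, so the formula works there. It does not carry over to a pain rating whose lowest value is 0.

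Zero is the natural answer when a stimulus does not hurt. The touch stimuli include a cotton wisp, the pinpricks start at 8 mN, and two of the four groups of 10 (20 of 40 participants) have no chronic pain. As written, the score then separates participants by whether they ever gave a 0. It no longer grades how sensitive they are. Someone with clear pain to two of three touch stimuli is recorded as having no allodynia.

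The fault can also pass unnoticed. In R, exponentiating the mean of the logs returns 0 without an error. An analyst who sees the problem late may improvise, and some improvised rules, such as dropping the zeros, reverse the ordering of participants.

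**Working it through.** The article states no numerical result for MPS, DMA or WUR, so there is no figure to reproduce. The check applies the stated formulas to values that the scale allows. All ratings below are invented for illustration.

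**1. Geometric mean.** GM = (x₁ × x₂ × … × xₙ)^(1/n).

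| Ratings | GM as written | Arithmetic mean |
|---|---|---|
| Pinprick 1, 2, 5, 8, 12, 20, 35 | 6.80 | 11.9 |
| Pinprick 0, 2, 5, 8, 12, 20, 35 | 0 | 11.7 |
| One 0 and thirty-four ratings of 100 | 0 | 3400/35 = 97.1 |
| Touch 0, 0, 0 | 0 | 0 |
| Touch 0, 0, 40 | 0 | 13.3 |
| Touch 0, 30, 60 | 0 | 30 |

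Changing one rating from 1 to 0 moves the arithmetic mean by 0.14 (1/7) and the geometric mean from 6.80 to 0. The last three rows differ clinically but receive the same score.

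**2. Dropping zeros.** Touch ratings 0, 0, 40 would score 40, above ratings 10, 20, 40, which score (8000)^(1/3) = 20. The less sensitive participant ranks higher.

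**3. How many participants?** The inputs needed are the number of ratings k and the chance p that a rating is 0. The article gives neither. Treating ratings as independent with a common p, the share with at least one 0 is 1 − (1 − p)^k:

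| k (assumed) | p = 5% | p = 10% | p = 20% | p = 50% |
|---|---|---|---|---|
| 3 (one rating per touch stimulus) | 14% | 27% | 49% | 88% |
| 7 (forces doubling from 8 to 512 mN, one rating each) | 30% | 52% | 79% | 99% |

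These figures are not estimates for this study, for two reasons.

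- Some zeros are correct. A person with no pain from any touch should score 0. Only mixed ratings are mis-scored: 1 − (1 − p)^k − p^k. With k = 3 and p = 50% this is 1 − 0.125 − 0.125 = 75%, not 88%.
- Ratings are not independent. If half the participants rate every touch 0 and half rate none 0, p is again 50%, DMA is 0 in 50%, and no score is wrong. Conversely, if everyone rates the wisp 0 and the other two stimuli above 0, p is only 1/3 and every DMA score is wrongly 0.

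The affected share could therefore lie anywhere from none to all.

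**4. Dependence on the constant.** For pinprick ratings 0, 2, 5, 8, 12, 20, 35:

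| Constant c | GM after adding c to all | The same, minus c |
|---|---|---|
| 0.01 | 3.53 | 3.52 |
| 0.1 | 4.96 | 4.86 |
| 0.5 | 6.58 | 6.08 |
| 1 | 7.69 | 6.69 |

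The result roughly doubles across reasonable constants, so a constant chosen after seeing the data could shift the results.

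**5. Wind-up ratio.** WUR = mean(series) / mean(single), five runs each. If all five single ratings are 0, a series mean of 11 gives 11/0 and a series mean of 0 gives 0/0; both are undefined. One isolated 0 does no harm. A small denominator is unstable: single ratings 0, 0, 0, 0, 1 (mean 0.2) with a series mean of 11 give 11/0.2 = 55. Under independence, the chance that all five are 0 is p⁵: 3%, 17% and 59% at assumed p of 50%, 70% and 90%.

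**The case against.** The strongest reply is that the article condenses a longer document and bases its testing on a published protocol. Zero handling before logging is the kind of detail that such a source, or an analysis plan, may supply. This cannot be ruled out, and it is a reason not to claim that the final scores will be wrong. It does not remove the point. The article states the scoring formula outright, and the formula fails on values that the article's own scale permits. Basing the testing on another protocol does not tell the reader that its scoring rules are all adopted.

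It can also be said that these are a few of many sensory parameters in exploratory analyses, that the primary aim is feasibility and acceptability, and that ratings are recorded per stimulus, so scores can be recomputed. All of that stands and limits the severity.

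Two stronger readings are tempting. A reader might infer that most MPS and DMA scores will be 0 and that the later sample size will rest on artefacts. The documents do not support this: the rating counts and zero rates are not given, some DMA zeros are correct, and no statement says that the spread of these two scores will drive the sample size. A reader might also infer that the wind-up ratio will be lost mainly in controls and so bias group comparisons. The documents give no basis for that either. The ratio fails only if all five ratings at 256 mN, in the upper part of the 8–512 mN range, are 0, and averaging before dividing already protects against isolated zeros.

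**Conclusion.** The point holds with moderate severity. As written, a single rating of 0 sets MPS or DMA to 0 whatever the other ratings are, so participants with mixed ratings cannot be told apart from those with no pain. This follows from the stated formula and scale alone and needs no assumption. The number of participants affected cannot be derived from the article, and the percentages under working only illustrate assumed inputs.

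The wind-up ratio has a smaller, related gap: it is undefined when all five single-stimulus ratings are 0.

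The consequence is confined to secondary, exploratory outcomes that inform the definitive study's design. The primary feasibility and acceptability outcomes are unaffected. If the full protocol or analysis plan already holds a zero rule, the remedy is simply to state it with the scoring formula.

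**What to change.** 1. State one zero rule for MPS and DMA before analysis and apply it to every participant. Either add a single named constant to every rating before logging and then back-transform (subtracting the constant at the end, so that an all-zero set still scores 0), or use the arithmetic mean.
2. Report the option not chosen as a sensitivity analysis. This is needed because the score depends materially on the constant.
3. For DMA, also report the proportion of participants with any touch rating above 0.
4. For wind-up, keep the ratio, report how many participants have an undefined value, and give the series-minus-single difference alongside, which is defined for everyone.

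The cost is a few sentences of scoring rules and a few lines of code on ratings already being collected. No extra testing or participants are needed. The drawback is that a constant or an arithmetic mean is partly a convention, which is why it should be fixed in advance and the alternative shown.

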There are a number of potential explanations for the relationship between ACEs, chronic pain and multimorbidity. From epidemiological studies, we know that these include social vulnerability^21^ and shared genetic vulnerability.^22^ However, other study designs can provide further insights into underlying mechanisms and may help identify potential targets for intervention. Psychophysical measurements may provide additional insights: while pain is a subjective experience, it is possible to derive objective pain measurements by using validated structured techniques.

Quantitative sensory testing (QST) is a structured method of assessing sensory pathways, deriving numerical measurements from subjective sensations. QST tests can be either static or dynamic; static QST evaluates the basal state of the nociceptive system through measurement of sensory/pain thresholds, while dynamic QST evaluates mechanisms of pain processing by using more complex stimulation of the somatosensory system.^23 24^ Studies utilising static QST assessments have reported lower pain thresholds in people with a history of physical or sexual abuse^25 26^ and in those with a history of psychological trauma.^27 28^ Some studies utilising dynamic QST assessments have reported altered pain processing in people with a history of childhood trauma^29^ or ACEs,^30^ though others have reported no relationship.^31 32^ One of the challenges is that the methods of ACE assessment and the QST protocols used vary between studies.

QST is well-established in pain research in both adult and paediatric populations, but to our knowledge, the QST profiles of individuals with multimorbidity have not been investigated. Understanding how these sensory parameters may vary based on ACE exposure may provide insights into the mechanisms that underpin the associations between ACEs, multimorbidity and chronic pain that are repeatedly seen in epidemiological studies. Our hypothesis is that exposure to ACEs is associated with lowered QST thresholds (ie, experience of pain with milder stimuli) and that this association is stronger in adults with multimorbidity and/or chronic pain. This is based on the higher prevalence of chronic pain found in people who have experienced ACEs and subsequent LTCs.^20 33 34^

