Cardiovascular disease	Stroke
	Coronary artery disease
	Heart failure
	Peripheral artery disease
	Heart valve disorders
	Arrhythmia
	Venous thromboembolic disease
	Aneurysm
	Hypertension (treated and untreated)
Metabolic and endocrine diseases	Diabetes
	Addison’s disease
	Cystic fibrosis
	Thyroid disorders
Respiratory disease	Chronic obstructive pulmonary disease
	Asthma
	Bronchiectasis
Neurological disease	Parkinson’s disease
	Epilepsy
	Multiple sclerosis
	Paralysis
	Transient ischaemic attack
	Peripheral neuropathy
Cancer	Solid organ cancers
	Haematological cancers
	Metastatic cancers
	Melanoma
	Benign cerebral tumours that cause disability
Mental and behavioural disorder	Dementia
	Schizophrenia
	Depression
	Anxiety
	Bipolar disorder
	Drug or alcohol misuse
	Eating disorder
	Autism
	Post-traumatic stress disorder
Musculoskeletal disease	Connective tissue disease
	Osteoarthritis
	Long-term musculoskeletal problems due to injury
	Osteoporosis
	Gout
Digestive disease	Chronic liver disease
	Inflammatory bowel disease
	Chronic pancreatic disease
	Peptic ulcer
Urogenital disorder	Chronic kidney disease
	End-stage kidney disease
	Endometriosis
	Chronic urinary tract infection
Haematological disorder	Anaemia (including pernicious anaemia and sickle cell anaemia)
Eye disease	Vision impairment that cannot be corrected
Ear disease	Hearing impairment that cannot be corrected
	Meniere’s disease
Infectious disease	HIV infection and AIDS
	Chronic Lyme disease
	Tuberculosis
	Post-acute COVID-19
Congenital disease	Congenital disease or chromosomal abnormalities

Adapted from Ho *et al*.^37^Ho et al. (2022).

ICD-10International Classification of Diseases (10th Revision)

**Table 2 T2:** Inclusion and exclusion criteria

Chronic pain with multimorbidity group	Chronic pain without multimorbidity group	Multimorbidity without chronic pain group	Control group
Inclusion criteria: Age ≥18 years Has ≥1 of the LTCs listed in table 1 Has a diagnosis of chronic pain AND/OR has had persistent or recurring pain lasting >3 months	Inclusion criteria: Age ≥18 years Has a diagnosis of chronic pain AND/OR has had persistent or recurring pain lasting >3 months	Inclusion criteria: Age ≥18 years Has ≥2 of the LTCs listed in table 1	Inclusion criteria: Age ≥18 years

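### All sensory testing is on the upper limb wherever the chronic pain is, and the article describes no marking of painful test sites, so in those participants local and general sensitivity cannot be separated

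*Protocol article*

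**What the plan says.** Table 2 of the Protocol article (Recruitment) defines the two chronic pain groups without reference to body site: "Has a diagnosis of chronic pain AND/OR has had persistent or recurring pain lasting >3 months". The same condition excludes people from the multimorbidity-only group and the control group.

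Under Procedure, every test is on the upper limb, but the sites are not all fixed in the same way:

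- **Pressure pain:** one site with no alternative. "The pressure pain threshold (PPT) will be measured at the thenar eminence with an algometer".
- **Thermal tests:** a choice of site. "Thermal detection and pain thresholds will be measured at the forearm or hand using a Modular Sensory Analyser". Mechanical detection, mechanical pain, stimulus response and wind-up have the same choice.
- **Vibration:** also a choice. "The vibration detection threshold (VDT) will be measured at a bony prominence at the wrist or elbow".
- **CPM:** sides follow hand dominance. "The participant will be asked to lower their non-dominant hand into a cold water bath", and the test stimuli go on the dominant arm.

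On sides, the article says: "Each test will be performed bilaterally, with the exception of the CPM test, which will be performed on one side only". It does not say how the two sides are combined.

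Before QST, participants complete a questionnaire on "Chronic pain, using the UK Biobank Pain Web Questionnaire". The article does not say whether it captures pain location, or whether location is used in testing or analysis. The Introduction gives static thresholds a general meaning: "static QST evaluates the basal state of the nociceptive system through measurement of sensory/pain thresholds".

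**The concern.** A threshold describes the general state of the nociceptive system only if the tested tissue is not itself a source of pain. With back pain and a pain-free hand, the reading is remote from the problem and serves that purpose. With chronic pain in the thumb, wrist or forearm, the reading mixes general sensitivity with local tenderness. The article describes nothing that tells the two kinds of reading apart.

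The mixing is one-sided. Chronic pain at the tested site can occur only in the two pain groups, and local tenderness lowers pain thresholds, which is the hypothesised direction. At stake are the pain versus no-pain comparison of thresholds and the preliminary estimates that, under Statistical analysis, are to inform the design and sample size of a definitive study.

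**Working it through.** **Inputs from the article.** Four groups of 10 give 4 × 10 = 40, which matches the stated total: 20 participants with chronic pain and 20 without. The article gives no significance level, power, effect size, SD, share with pain at a test site or size of local shift.

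**Assumed inputs.** q is the share of pain-group participants with pain at the tested site, taken as 10–40%. d is the drop in threshold at such a site, taken as 0.5–1.0 SD.

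**1. Shift in the pain versus no-pain contrast.** With no general difference between groups, the expected spurious difference is q × d if both sides are painful. If pain is one-sided and the two sides are averaged, it is q × d ÷ 2.

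| q | both sides, d = 0.5 | both sides, d = 1.0 | one side, d = 0.5 | one side, d = 1.0 |
|---|---|---|---|---|
| 10% | 0.05 | 0.10 | 0.025 | 0.05 |
| 20% | 0.10 | 0.20 | 0.05 | 0.10 |
| 30% | 0.15 | 0.30 | 0.075 | 0.15 |
| 40% | 0.20 | 0.40 | 0.10 | 0.20 |

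**2. Would the study notice?** The 95% CI half-width for 20 v 20 is 1.96 × √(2/20) = 0.62 SD, so none of these shifts would stand out from noise in the group means. Affected participants are nevertheless likely to be present. The binomial chance that at least 3 of the 20 pain-group participants are affected is 0.323 at q = 10%, 0.794 at 20% and 0.965 at 30%.

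**3. ACE slope within the pain groups.** Write threshold = a + b × ACE − d × L, where L = 1 if the tested site is painful. A regression that omits L estimates b − d × cov(L, ACE) ÷ var(ACE). If L is unrelated to ACE count, the covariance is zero and the slope is unbiased; local pain only adds noise. A slope pooled over all four groups without a group term could absorb part of the shift in step 1 if ACE counts differ between groups. The article does not say whether such a model will be fitted.

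**4. Added spread.** The extra variance in the pain groups is q(1 − q)d²:

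- low end: 0.10 × 0.90 × 0.25 = 0.0225
- high end: 0.40 × 0.60 × 1.00 = 0.24

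The SD rises by √1.0225 − 1 = 1% to √1.24 − 1 = 11%.

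**5. Planning.** This step applies only if the definitive study is sized on the pain contrast. With n per group = 2 × (1.96 + 0.84)² ÷ Δ² (two-sided 5%, 80% power), an assumed true Δ of 0.5 SD needs 63. A contrast shifted by 0.05 to 0.40 SD, to 0.55 or 0.90 SD, would suggest 52 or 20.

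**6. CPM.** The formula in step 1 does not carry over. Absolute CPM is a before-minus-during difference at the same place, so a constant local shift cancels. It does not cancel in the percentage, which divides by the baseline threshold. A painful conditioning hand may also change how the water bath is felt.

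**The case against.** The strongest reply has four parts.

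- **This is a condensed article.** Its QST is based on a cited network protocol that is not shown, and site rules may sit in the full protocol. That stands as far as analysis rules go. The Statistical analysis section offers examples only, so nobody can say from the text that painful-site and remote readings will be pooled.
- **Most sites are not fixed.** A reader might infer that every test has one mandatory location. Only pressure pain does; CPM fixes the sides. Elsewhere a tester could move away from a painful area. The article does not say that this is the purpose of the choice, and unrecorded avoidance would put some pain participants at different sites from controls.
- **Safeguards may already exist.** The pain questionnaire may record location, and testing both sides allows a side-to-side check. Both are possible, but the article links neither to the tested site and side. Group 2 also excludes every Table 1 condition, including osteoarthritis, gout and peripheral neuropathy, so q may be lower there than in group 1.
- **QST is secondary and exploratory, and a common remote site is a reasonable measure for pain elsewhere.** Both are true. The upper-limb choice is not itself an error.

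One point is not answered by deferring to an analysis plan. There is a single session and no follow-up, so pain at a test site that was not recorded at testing cannot be recovered by a later analysis rule.

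**Conclusion.** The point holds for pain-group participants whose pain involves the tested site. In them, local and general sensitivity cannot be separated on the procedure as described, and the pain versus no-pain contrast can be biased in the hypothesised direction. On the assumed inputs the bias is 0.05–0.40 SD with pain on both sides, or about 0.025–0.20 SD if pain is one-sided and sides are averaged. The range runs from negligible to material because neither q nor d is in the article.

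Two stronger readings are tempting and not supported:

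- **That the design manufactures a stronger ACE association in chronic pain.** Step 3 shows that the slope within the pain groups is biased only if local pain is related to ACE count, and the article gives no evidence on that.
- **That the variance passed to the definitive study is badly inflated.** The rise in SD is 1–11%, and a definitive study with the same sites and population would face the same spread. It would also meet the same shift, so the harm there is mainly to interpretation.

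The change is worth making because it costs little. It concerns the secondary aim and later planning, and leaves the primary feasibility and acceptability outcomes untouched.

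**What to change.** Add one yes/no item per test site and side to the QST form: *Is this site painful now or part of your chronic pain?* Include the CPM test arm and the conditioning hand, whose sides cannot switch under the dominance rule. Then:

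- keep all participants in the main exploratory analysis;
- report how often a test site was painful, by group, as a feasibility result;
- show the group comparisons and the ACE analyses with and without painful-site readings;
- use pain-free-side values as a sensitivity analysis only. As the main rule, this would select sides in pain participants but not in controls. Setting aside those painful on both sides could remove the people with widespread sensitivity whom the hypothesis concerns.

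The cost is one extra form line and one extra analysis, with no extra test. The sensitivity analysis will have a smaller n. Participants tested before the item is introduced should be reported as not recorded.
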